## Abstract

**Background:**

Even though there are continually upgraded recommendations for managing sepsis, such as "Surviving Sepsis Campaign: international guidelines for management of severe sepsis and septic shock", mortality is still high. Si-Ni-Tang, a remedy documented in Shanghan Lun, a medical collection from ancient China, is used for treating patients with sepsis and septic shock. Using a well-designed clinical trial, we are eager to survey the effectiveness of the concurrent use of this remedy in restoring these patients' hemodynamic status, or "Yang Qi".

**Methods/Design:**

Patients admitted to our medical intensive care units with the diagnosis of septic shock, defined as persistent hypotension induced by sepsis despite adequate fluid resuscitation, are eligible for participation. The inclusion criteria include: age from 20 to 85 years, conditions meeting the definition of septic shock, use of vasopressors within 24 hours of entering the study, and use of a nasogastric tube for feeding. The enrolled patients are randomly allocated either to the Si-Ni-Tang group or the placebo group. The prescription of the trial drugs (Si-Ni-Tang/placebo) is 2.25 grams 4 times a day for 7 days or till shock reversal (if shock reversal occurs in less than 7 days). Data, including duration of vasopressor infusion, gender, age, co-morbidities, APACHE II score, predicted mortality, ICU mortality, ICU length of stay, hospital mortality, hospital length of stay, source of sepsis, and culture results, are collected for the following analysis.

**Discussion:**

Si-Ni-Tang is composed of processed *Zingiber officinale*, *Glycyrrhiza uralensis*, and *Aconitum carmichaeli*. *Zingiber officinale *and *Glycyrrhiza uralensis *are found to have the ability to reduce pro-inflammatory cytokine production, to inhibit lipopolisaccharide-induced macrophage activation and function, and to lessen the bacterial load and suppress acute and chronic inflammation. *Aconitum carmichaeli *is known to have vasopressor activity, and positive chronotropic and inotropic effects. As this remedy has a potential benefit in treating septic shock patients, we designed a double-blind, prospective, randomized controlled trial and would like to publish the results and conclusions later.

**Trial Registration:**

ClinicalTrials.gov: NCT01223430

## Background

Sepsis is an infectious disease, usually caused by bacterial infection, with systemic manifestations. Severe sepsis is defined as sepsis with organ dysfunction or tissue hypoperfusion related to sepsis. If the disease progresses to persistent hypotension, even with adequate fluid resuscitation, the presentation is known as septic shock.

Severe sepsis, and if further deteriorated, septic shock, are important issues for healthcare workers. Even though the recommendations for managing sepsis and septic shock, such as "Surviving Sepsis Campaign: international guidelines for management of severe sepsis and septic shock"[1], are continually upgraded, mortality due to sepsis and septic shock in the intensive care units is still high.

We may not know initially the exact etiology of the septic shock when treating the patients, but maintaining an adequate hemodynamic status in order to keep these patients with organ perfusion well is always the main issue for intensivists.

The history of Chinese medicine can be traced back thousands of years. Certainly, the theory and application of Chinese medicine in treating patients with severe infection have been documented in several Chinese medical books. The presentation of the septic shock patient is characterized as "depletion of Yang Qi", meaning little energy and very weak pulse.

When treating patients diagnosed with septic shock, the optimal approach we will take will be to follow recently proposed guidelines. However, there is still much research devoted to finding a better way to improve patient outcome. Herbal or Chinese medicine has been investigated in the treatment of infectious disease and shock[2]. Many remedies to treat sepsis or septic shock have been documented in ancient Chinese medical books or literature. Si-Ni-Tang, for example, documented in Shanghan Lun, a medical collection from ancient China, is used for treating patients with shock, heart failure, severe watery diarrhea and poor extremity circulation. It is considered a good choice to treat patients who suffer from infectious disease complicated with hemodynamic instability.

Si-Ni-Tang is manufactured from and composed of processed *Zingiber officinale*, *Glycyrrhiza uralensis*, and *Aconitum carmichaeli*. Using a well-designed clinical trial, we are eager to survey the effectiveness of concurrent use of this remedy in restoring "Yang Qi". That is to say, we want to know whether Si-Ni-Tang can shorten the duration of the shock status. The purpose of this study is to determine whether the simultaneous use of a traditional Chinese medicine, Si-Ni-Tang, is more effective in the treatment of septic shock patients. Only by conscientiously performing studies and pursuing positive outcomes can we push Chinese medicine onto the stage. Certainly, finding the best way to benefit people and patients with septic shock is the ultimate goal of our study.

## Methods/Design

The study is designed as a double-blind, prospective, randomized controlled trial. It has been approved by the ethics committee. Our study procedures and informed consent were reviewed by the Institutional Review Board of Changhua Christian Hospital beginning in Jan. 2010. There were four revisions before the study procedures and informed consents were finally approved by the third Institutional Review Board Committee on Aug. 10, 2010.

All participating patients are randomized using a computerized block randomization schedule with a multiple block size of four. 120 patients (30 blocks) were randomly (same chance) generated that were kept in sequentially numbered opaque envelopes. Researchers and patients are blinded to treatment allocation; the only un-blinded individual is the statistician responsible for randomization process. The treatment assignments are balanced within each block. Each block contains 4 patients with 2 patients for Si-Ni-Tang group, and 2 patients for placebo group (same chance).

Our study is directed by the Graduate Institute of Integrated Medicine, College of Chinese Medicine, China Medical University and is conducted in the medical intensive care units in Changhua Christian Hospital, a medical center in central Taiwan. The drugs used in the trial, whether Si-Ni-Tang or placebo, are both manufactured and provided by a pharmaceutical company that meet the requirements of Good Manufacturing Practice. All important drug information, including ingredient composition, heavy metals, etc., is provided by the same company.

According to the GUIDELINE ON CLINICAL TRIAL OF NEW CHINESE MEDICINE promulgated by the Department of Health, Executive Yuan, Taiwan on Feb. 5, 2008, we are allowed to investigate directly the therapeutic efficacy of the Chinese medicines listed in classical Chinese pharmacopoeias, due to the long-term experience and widespread clinical use of these medicines. The drug used in our trial, Si-Ni-Tang, an example of Chinese medicines listed in classical Chinese pharmacopoeias, is regarded as safe and effective for patients with shock. However, it has been criticized for lacking adequate evaluation through clinical trials supported and conducted according to the principles of modern clinical trials. To evaluate the actual benefit and the possible risk, we designed this double-blind, prospective, randomized controlled trial.

Our study is being carried out somewhat like phase 2 studies in clinical trials. Phase 2 studies are set forth to evaluate the effectiveness of drugs in participants with a certain disease or condition. We assume that the mean duration of vasopressor use of the Si-Ni-Tang group is 3 hours shorter than that of the placebo group, with a standard deviation of 6.5 hours. Under the setting of alpha = .05 and power = 80%, the calculated sample size of each group is around 60. This is why we plan to enroll 120 participants.

Sepsis is an infectious disease, usually caused by bacterial infection, with systemic manifestations. Sepsis-induced hypotension is defined as a systolic blood pressure less than 90 mmHg or mean arterial pressure less than 70 mmHg. Septic shock is defined as persistent hypotension induced by sepsis, despite adequate fluid resuscitation. We plan to enroll 120 patients who have been admitted to our medical intensive care units with the diagnosis of septic shock. The flow chart of the study is illustrated as Figure 1.

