**Figure 1 F1:**
[figure not shown]
**Enrolment Flowchart**. The figure illustrates how the participants are enrolled and allocated.

Eligible patients must fulfill all the following requirements: age from 20 to 85 years, a disease diagnosis meeting the definition of septic shock, use of vasopressors now and an initiation of vasopressor use within 24 hours of entering the study, use of a nasogastric tube for feeding, and informed consent obtained from either the patients or their relatives.

Exclusion criteria are an extremely poor gastrointestinal function and an inability to tolerate diet feeding, acute myocardial infarction, evidence of major bleeding, expected or scheduled surgical intervention in the subsequent one week, use of 2 or more than 2 kinds of vasopressors upon entrance into the study, and patients who have received digoxin for arrhythmia within the past one week.

The treatment for the patients with septic shock in our hospital adheres to the Surviving Sepsis Campaign: International guidelines for management of severe sepsis and septic shock 2008. Our study uses block randomization with a block size of 4 and an allocation ratio of 1:1. After enrolment, the eligible patients are either allocated to the Si-Ni-Tang group or the placebo group. The prescription of the trial drugs is 2.25 grams 4 times a day (9 grams per day) for 7 days or till shock reversal (if shock reversal occurs in less than 7 days). Shock reversal is defined as the discontinuation of norepinephrine or dopamine for at least 24 hours.

We will collect the following data from each participant: gender, age, co-morbidities, APACHE II score, predicted mortality, ICU mortality, ICU length of stay, hospital mortality, hospital length of stay, source of sepsis (pulmonary, gastrointestinal, renal or others), culture results (Gram-positive, Gram-negative or mixed) and duration of vasopressor infusion. Shock reversal and time to cessation of vasopressor use would be the primary outcome measurements.

Baseline variables will be evaluated for balance between the two groups using the Student's t-test for unpaired data for the comparison of continuous variables and the Pearson's chi-squared test to compare categorical variables.

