The effect of Si-Ni-Tang treatment on time to cessation of vasopressor use is estimated, first, from Kaplan-Meier curves and log-rank test for median time, and second, from adjusted Cox proportional hazards regression models for potential confounders (age, APACHE II score at baseline, source of sepsis, co-morbidities). Corresponding hazard ratios along with their 95% confidence intervals are reported. Patients who died before cessation of vasopressor use are treated as censored. Analysis is performed on the intention to treat population.

There is no planned subgroup analysis anticipated. Only primary and secondary outcome measures will be analyzed. However, all of the variables which are found to be important predictors of shock reversal and adverse outcome will be used for stratifications for post-hoc analysis (relative risks will be estimated for the major outcomes using multivariate Poisson regression adjusting for covariates).

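### The 80% power claim comes from a comparison of mean durations and does not carry over to the planned log-rank/Cox analysis with deaths censored

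*Protocol article*

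**What the plan says.** All references are to the protocol article, Methods/Design.

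- **Sample size paragraph.** Time on vasopressor under Si-Ni-Tang is assumed to average "3 hours shorter than that of the placebo group, with a standard deviation of 6.5 hours". Alpha is set at .05 and power at 80%. From these inputs the authors conclude that "the calculated sample size of each group is around 60", hence 120 patients. The paragraph does not say whether alpha is one- or two-sided, gives no source for the SD, and makes no allowance for death or censoring.
- **Outcome paragraph (after Figure 1).** Shock reversal and time to cessation of vasopressor are the primary outcomes.
- **Statistical analysis paragraph.** Time to cessation is analysed by "Kaplan-Meier curves and log-rank test for median time", then by adjusted Cox regression with hazard ratios. Patients who die before cessation are censored.
- **Treatment paragraph.** Trial drug is given "for 7 days or till shock reversal (if shock reversal occurs in less than 7 days").

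The Background describes mortality in this population as still high but gives no rate.

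**The concern.** The trial is sized for one analysis and will be tested with another. A comparison of means uses a difference, an SD and a complete duration for each patient. A log-rank or Cox analysis draws its information from observed cessations and from the ratio of cessation rates. A patient who dies on vasopressor adds time at risk but no event, so 120 patients will give fewer than 120 events in a population with high mortality.

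The 80% figure is the only power statement for a primary outcome. If it does not hold under the planned test, readers of a null result would take it as stronger evidence against a 3-hour benefit than it is.

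**Working it through.** **Inputs from the article:** difference 3 h, SD 6.5 h, alpha .05, power 80%, allocation 1:1, about 60 per group. **Not in the article, so assumed:** control mean, shape of the duration distribution, proportion dying on vasopressor.

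**1. Reproduce the stated size.** For two means, n per arm = 2 × (z_alpha + z_beta)² × (SD/difference)², with (6.5/3)² = 4.694.
- One-sided: 2 × (1.645 + 0.842)² × 4.694 = 58.1, so 59 per arm (also 59 with the t distribution).
- Two-sided: 2 × (1.960 + 0.842)² × 4.694 = 73.7, so 74 per arm (75 with the t distribution).

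The stated figure is therefore the one-sided result with no inflation for patients without a complete duration.

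**2. Power of 60 per arm for the means comparison.** The standardised difference is 3 / (6.5 × √(2/60)) = 2.53. Two-sided power is 71%; one-sided power is 81%.

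**3. Log-rank power on the plan's own figures.** This was simulated with 60 per arm, a 3 h shorter mean and SD 6.5 h in both arms, using normal or lognormal durations with assumed control means of 12 to 40 h. Deaths were placed at random times before the patient's cessation. Values are approximate, to about one percentage point.

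| Die on vasopressor (assumed) | Two-sided | One-sided |
|---|---|---|
| None | 57-66% | 68-76% |
| 30% | 45-54% | 57-66% |

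**4. Hazard ratio that 120 patients can detect.** With 1:1 allocation, HR = exp(2 × (1.960 + 0.842) / √events) for 80% two-sided power.

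| Deaths on vasopressor (assumed) | Events | Detectable HR |
|---|---|---|
| 0% | 120 | exp(5.604/10.954) = 1.67 |
| 30% | 84 | exp(5.604/9.165) = 1.84 |
| 40% | 72 | exp(5.604/8.485) = 1.94 |
| 50% | 60 | exp(5.604/7.746) = 2.06 |

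**5. The SD.** Under normality, 6.5 h puts 95% of durations in a band 2 × 1.96 × 6.5 = 25.5 h wide. The treatment course may run to 7 × 24 = 168 h. The SD looks small, but this is not an arithmetical contradiction.

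**The case against.** **The loss may be modest.** Sizing a time-to-event trial from means is a common approximation, the study calls itself somewhat like phase 2, and the test may have been meant as one-sided. If treatment shortened every duration by the same proportion, with lognormal durations and an assumed control mean of 12 h, log-rank power without deaths would be about 80% two-sided (87% one-sided). That case is real, but it makes the treated arm's SD 6.5 × 9/12 = 4.9 h, below the single SD the plan states, and with 30% dying it falls to 69% two-sided. With SD 6.5 h in both arms, one-sided testing without deaths reaches at most about 76%.

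**A reader might infer three stronger conclusions, which the article does not support.**

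- *That power is only 5-11%.* This follows from assuming exponential durations with means of 24 to 72 h. An exponential distribution has SD equal to its mean, so the assumption replaces the stated 6.5 h with 24 to 72 h. It is a different SD, not a consequence of the change of test.
- *That SD 6.5 h is incompatible with the design.* Seven days is a ceiling, since treatment stops at shock reversal, and patients on two or more vasopressors at entry are excluded. Nor can the entry criterion ("use of vasopressors now and an initiation of vasopressor use within 24 hours of entering the study") be used to add spread to the 6.5 h. If duration runs from infusion start, the moment of entry only divides a fixed total; if it runs from randomisation, time before entry is not in the outcome.
- *That the outcome includes up to 24 h which treatment cannot affect.* This needs a clock starting at infusion. The article does not state the time origin, which a full protocol or SAP may do.

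**Conclusion.** The mismatch stands: the stated 80% power belongs to a one-sided comparison of means with every patient contributing, not to the log-rank/Cox analysis with deaths censored. On the plan's own difference and a common SD, two-sided log-rank power is about 57-66% without deaths and about 45-54% if 30% die on vasopressor. One-sided testing narrows the gap but does not close it.

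The mismatch itself is read directly from the article. The sizes rest on assumed control means, distribution shapes and death rate, and on SD 6.5 h being right. The article gives no source for that SD; if the true SD is larger, power for 3 h is lower, but nothing in the article says by how much. An unseen SAP could add detail but would not make the published justification for 120 patients correct. Should be fixed; the design and the planned test can stay as they are.

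**What to change.** Keep 120 patients and rewrite the justification:

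1. Remove the claim of 80% power for a 3 h difference.
2. State whether alpha .05 is one- or two-sided.
3. State the expected number of cessations after allowing for deaths on vasopressor, and the hazard ratio detectable at 80% two-sided power for that number (second table above). If the death rate is uncertain, show the range.
4. Give the source of SD 6.5 h, or check it on blinded pooled data from patients already enrolled (the Discussion says the trial is running) and report the result.

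The cost is wording and one blinded calculation. No extra patients are needed. The stated detectable effect becomes less favourable.

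### The 60 per group reproduces only with an undeclared one-sided .05 test; read two-sided, in line with the 95% intervals, the same inputs give about 71% power for a comparison of means

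*Protocol article*

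**What the plan says.** In Methods/Design the protocol article sizes the trial as a comparison of two means. The duration of vasopressor use with Si-Ni-Tang is assumed to be "3 hours shorter than that of the placebo group, with a standard deviation of 6.5 hours". It continues: "Under the setting of alpha = .05 and power = 80%, the calculated sample size of each group is around 60", and then "This is why we plan to enroll 120 participants". Allocation is equal: "block randomization with a block size of 4 and an allocation ratio of 1:1". The paragraph does not say whether alpha is one-sided or two-sided.

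The analysis paragraphs, later in Methods/Design, name a log-rank test and then adjusted Cox models for time to cessation of vasopressors, with patients who die on vasopressors censored. On reporting they say: "Corresponding hazard ratios along with their 95% confidence intervals are reported". Neither the log-rank test nor the Cox model is described as one-sided, and no one-sided test is declared anywhere else in the article.

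**The concern.** Every input of the calculation is printed, so the figure can be checked directly. The usual two-sided calculation at .05 gives a clearly larger number than 60. The gap is too wide for rounding: 74 is 23% above 60 and 75 is 25% above it. The number appears only if the whole 5% error is spent on the favourable direction. The sample size and the reported inference then rest on different error rates.

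Two things are at stake. First, a reader who trusts the 80% would give a null result more weight than it deserves: for a two-sided comparison of means on these inputs, the chance of missing a true 3-hour effect is about 29%, not 20%. Second, open sidedness leaves room to choose it late. Moving from two-sided to one-sided .05 once results are known would double the false-positive rate in the favourable direction from 2.5% to 5%.

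**Working it through.** **Inputs**, all from Methods/Design: difference 3 h, SD 6.5 h, alpha .05, power 80%, allocation 1:1, 60 per group. Standardised difference d = 3/6.5 = 0.4615, so d² = 0.2130.

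**Formula for the size per group** (normal approximation): n = 2(z_alpha + z_power)²/d², with z_power = 0.842 for 80%.

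**Reproducing the plan's figure, one-sided .05** (z_alpha = 1.645):
- n = 2(1.645 + 0.842)²/0.2130 = 58.0, which rounds up to 59. The t-test version gives 58.7, also 59.
- This fits a statement of about 60.

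**Two-sided .05** (z_alpha = 1.960):
- n = 2(1.960 + 0.842)²/0.2130 = 73.7, which rounds up to 74. The t-test version gives 74.7, so 75.
- The total is 148 to 150, and the planned 120 is 28 to 30 short (28/148 = 19%; 30/150 = 20%).

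**Power at 60 per group.** The expected value of the test statistic is d·√(60/2) = 0.4615 × 5.477 = 2.528.

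| Test at .05 | Normal approximation | t-test |
|---|---|---|
| One-sided | Φ(2.528 − 1.645) = 81.1% | 80.7% |
| Two-sided | Φ(2.528 − 1.960) = 71.5% | 70.8% |

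**What 60 per group detects with 80% power, two-sided.** Normal approximation: 6.5 × √(2/60) × (1.960 + 0.842) = 3.32 h. The t-test version gives 3.35 h. Alternatively, with the difference held at 3 h, the SD would have to fall to about 5.87 h (normal approximation).

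**Other routes to 60 with a two-sided .05 test and 80% power:**
- Allowing for the efficiency of a rank test: 74/0.955 = 77.5, so 78 per group.
- A single-sample formula: 36.8, so 37.
- Adding a dropout allowance only raises the number (78 at 5% dropout).

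None of these gives 60.

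**Matching intervals to tests.** A 95% two-sided interval excludes the null value exactly when a two-sided 5% test rejects. A one-sided .05 test pairs with a 90% two-sided interval or a 95% one-sided bound. The analysis section specifies 95% intervals, which do not pair with the test that reproduces the sample size.

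**The case against.** The strongest reply is that nothing was miscalculated. The figure reproduces at one-sided .05, and the text gives that reading some support: the stated aim is to learn whether the remedy makes shock shorter, the assumed effect has a direction, and the study likens itself to phase 2, where one-sided screening tests are not unusual. A 95% interval sets a reporting format, not a rejection rule; trials with one-sided tests often print 95% intervals all the same. Naming a log-rank test fixes no side either. And sidedness is a detail that a condensed article may leave to a full protocol or analysis plan that is not shown.

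Much of this stands. A reader might infer that the sample size is a plain arithmetic mistake. The article does not support that, because the number follows from a definable, though undeclared, choice. A reader might also infer that the plan prints a two-sided test. It does not; that is an inference from the intervals and from convention.

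What does not stand is the step from a directional aim to a one-sided test. Every superiority calculation assumes an effect in a stated direction. A one-sided .05 test departs from convention and needs to be declared. The article also says that it wants to assess possible risk as well as benefit, which a test looking only for benefit serves poorly. Nor does the point rest on missing detail: the printed sample size and the printed intervals do not fit each other, and an unseen document declaring a one-sided test would leave that mismatch in place.

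**Conclusion.** The point holds in conditional form. The stated 80% power with about 60 per group is true only for a one-sided .05 test, which the article does not declare and which does not match its 95% intervals. Under the conventional two-sided reading the inputs need 74 to 75 per group, and 60 per group gives about 71% power (70.8% by t-test, 71.5% by normal approximation), some 9 points below the claim.

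This rests on three conditions: the printed 3 h and 6.5 h are taken as given, no patients are lost, and the two-sided reading is accepted.

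One stronger reading should be resisted: that the trial itself has 71% power, or will miss a true effect 29% of the time. Those figures describe a comparison of means. The planned primary analysis is log-rank and Cox with deaths censored, and the article gives neither event rates nor a hazard ratio from which its power could be derived. Neither 80% nor 71% is the power of that analysis.

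**What to change.** Keep the enrolment at 120. State that tests are two-sided at .05, in line with the 95% intervals, and replace the power statement with wording such as: *Sixty patients per group give about 71% power for a two-sided comparison of means at alpha .05, for a 3-hour difference and SD 6.5 h (80% for 3.35 h). This is not the power of the log-rank or Cox analysis.*

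If the design was pre-specified as one-sided, disclose that before unblinding, and align the primary test and the intervals with it. A one-sided rule should not be adopted for the first time now to justify the number. The Discussion says that the trial is already running, so either correction should be dated and made while the data are still blinded.

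The cost is a sentence or two and a less favourable power figure. No extra patients are needed, and the two-sided route leaves the planned analysis unchanged.
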